## **5. TREATMENT OF SUBJECTS**

### **5.1. Investigational product/treatment**

Subjects will receive either green tea or placebo in capsule form after their baseline measurement, which they have to consume daily for a period of twelve weeks. Subjects will visit the university three times (baseline, 6 weeks and 12 weeks) and three days before each visit faeces will be collected for analysing the gut flora and fat absorption. They will be asked to travel by public transport or car, in order to avoid physical activity that would increase REE. Subjects will arrive in fasted state at 08:30 h. They will empty their bladder before the test. After resting on a bed for 30 min, the REE and the substrate oxidation of the subjects will be measured for 30 min by means of an open-circuit, ventilated hood system.

Subjects will receive either green tea (250 mg/capsule [ $> 62.5$  mg EGCG +  $> 31.3$  mg caffeine], 3 capsules with each breakfast, lunch and dinner) or placebo (soy oil; 757 mg/capsule, 3 capsules with each breakfast, lunch and dinner) in capsule form after their baseline measurement, which they have to consume daily for a period of twelve weeks. The product information for the green tea and the placebo capsules can be found in the attachments. When specifying the placebo capsules the green tea extract is replaced with microcrystalline cellulose (270.5 mg per capsule in the green tea capsules vs 515.5 mg in the placebo capsules). Microcrystalline cellulose is refined wood pulp, and often used in vitamin supplement.

### **5.2. Use of co-intervention**

Subjects will be asked not to change their food pattern during the period of twelve weeks. They will be instructed to abstain from dairy products (like milk, cheese, pudding and yoghurt) to use less than 100 ml caffeine-containing beverages per day and to avoid probiotics.

## 6. METHODS

### 6.1. Study parameters/endpoints

#### 6.1.1. Main study parameter/endpoint

The primary endpoint of this study is the change in gut flora; ratio firmicutes/bacteroidetes, changes in total faecal fat and change in body weight.

Green tea may inhibit lipase activity, which is essential for lipid absorption. Faecal fat excretion will be measured to determine the lipid absorption.

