## SUMMARY

**Rationale:** Green tea might have positive effects for weight control and body composition via several approaches such as a positive effect on the gut flora, a decrease in fat absorption from the intestines and an increase in resting energy expenditure.

**Objective:** To investigate the long-term effects of green tea on gut flora, fat absorption, resting energy expenditure and body composition.

**Study design:** The study will be conducted in a randomized, placebo-controlled, double-blind parallel design with four groups consisting of control groups and green tea groups with normal weight subjects and obese subjects. At three time points (baseline, 6 weeks and 12 weeks) faeces are collected for analyzing the gut flora and fat absorption. Furthermore, measurements of resting energy expenditure and body composition will be conducted. Activity will be measured throughout 3 weeks.

**Study population:** a hundred healthy subjects (50 males and 50 females) with a body mass index (BMI) between 18.5-25 kg/m^2 and ≥30 kg/m^2 and aged between 18-50 years will be included in the study. All subjects will be non-smoking, weight stable, dietary unrestrained, not drinking tea and at most moderate alcohol and caffeine consumers. Subjects will be free of medication except for oral contraceptives use in women.

**Intervention:** Subjects will receive either green tea or placebo in capsule form after their baseline measurement, which they have to consume daily for a period of twelve weeks.

**Main study parameters/endpoints:** Gut flora composition, fat absorption, body composition and resting energy expenditure.

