## 2. OBJECTIVES

The objective of this study is to investigate the long-term effects of green tea on gut flora, fat absorption, resting energy expenditure and body composition. The primary aim of the present study is to examine whether green tea supplements affect fat metabolism, gut flora and body weight.

This primary objective implies that green tea increases faecal fat and decreases fat absorption, resulting in decrease in digestible energy of the diet. Green tea may inhibit lipase activity. Inhibition of digestive lipase activity could significantly affect dietary lipid absorption and could increase lipid excretion into the faeces. Faecal fat excretion will be measured to determine the lipid absorption (10).

Previous studies have shown comparable effects in animal studies (4-6). This study needs to determine whether green tea also increases faecal fat and lowers the fat absorption in humans and will test the hypothesis that the increase in faecal fat will be larger in the green tea conditions compared to the conditions without green tea.

Furthermore we will investigate whether green tea has positive effects on gut flora and will increase the relative proportion of *Bacteroidetes* to *Firmicutes* and that this change in *Firmicutes/Bacteroidetes* ratio will be larger in obese subjects compared to normal weight subjects. Metabolism of polyphenols by microbiota involves the cleavage of glycosidic linkages. Glycans, which are the product of glycosidic cleavage, are necessary for survival of the intestinal microbiota as a nutrient foundation. *Firmicutes* possess a disproportionately smaller number of glycan-degrading enzymes than *Bacteroidetes*. Furthermore, *Firmicutes* are more repressed than the *Bacteroidetes* by phenolic compounds' antimicrobial properties. The *Bacteroidetes* community prevails following dietary polyphenol intake and its fermentation to phenolic compounds, due to having more glycan-degrading enzymes, so this may thus be a mechanism by which dietary polyphenols exert their weight lowering effect (9).

Finally, we will investigate whether a supplementation with green tea polyphenols is proposed for weight loss via an increase in the resting energy expenditure and fat oxidation.

Four groups consisting of control groups and green tea groups with normal weight subjects and obese subjects will be applied in order to completely answer the research questions:

- Normal weight without green tea (NW/control)

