#### 4.4. Sample size calculation

The primary endpoint of this study is the change in gut flora and fat absorption.

For the sample size calculation the following formula was used:

$$N = 2 + (Z_{1-\beta} + Z_{1-\alpha/2})^2 \times \sigma^2 / (\mu_{GT} - \mu_{CONTROL})^2$$

Subject population size was calculated using G\*Power 3.1.2 where  $\alpha$  was 0.05,  $\beta$  was 0.95 using group mean body weight changes from past papers (12) to calculate the effect size, the population was finalized as 45 per group and an additional 5 (drop-out of 10%) will be included in the population size for any unforeseeable circumstances which may lead to subjects dropping out.

The calculated sample size will be:

|                    |           |           |
|--------------------|-----------|-----------|
| Means:             | u1 = 72.5 | u2 = 71.4 |
| Standard deviation | SD1= 1.4  | SD2= 1.7  |

Confidence interval is  $\alpha=0.05$ , for  $\beta=0.95$

$$N1 = N2 = 2 + (Z(1-\beta) + Z(1-\alpha/2))^2 \times \frac{(\sigma_1^2 + \sigma_2^2)}{(\mu_1 - \mu_2)^2}$$

45 people per condition (two conditions; green tea and placebo).

Taking a drop-out of 10% into account, 50 subjects will be included per condition and herewith 100 subjects will be included in the experiment.

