#### 6.1.2. Secondary study parameters/endpoints

- Resting energy expenditure (REE)
- Respiratory quotient (RQ)
- Three frequency eating questionnaire (TFEQ)
- Body composition: BMI, body fat percentage, fat mass index (FMI)
- Body fat distribution: waist circumference, waist-to-hip ratio (WHR)

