### **8.2. Univariate analysis**

The Statistical Package for the Social Sciences (SPSS) will be used to perform univariate analyses. ANOVA will be performed to determine possible differences in gut flora, fat absorption, REE, activity and body composition between the four groups, with time (baseline, 6 weeks, 12 weeks) as the within-subject factor and group (normal weight-GT, normal weight-control, obese-GT, obese-control) as the between-subject factor. Post hoc, a Scheffe's *F* test will be applied. Statistical significance will be set at  $p < .05$ .

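### The protocol gives about three conflicting primary-endpoint sets, powers only body weight (missing from the endpoint sentence of Section 4.4), and states no rule for claiming success across endpoints

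*Protocol*

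**What the plan says.** Four places in the protocol describe what the trial is mainly about.

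- Summary, main endpoints: "Gut flora composition, fat absorption, body composition and resting energy expenditure".
- Section 2: the opening sentence names the same four domains as the Summary. The text then narrows: "The primary aim of the present study is to examine whether green tea supplements affect fat metabolism, gut flora and body weight".
- Section 4.4: "The primary endpoint of this study is the change in gut flora and fat absorption".
- Section 6.1.1: "The primary endpoint of this study is the change in gut flora; ratio firmicutes/bacteroidetes, changes in total faecal fat and change in body weight".

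Section 6.1.2 lists REE and the body composition measures (BMI, body fat percentage, fat mass index) as secondary.

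The sample size in Section 4.4 was obtained "using group mean body weight changes from past papers (12) to calculate the effect size". The inputs are means of 72.5 and 71.4, SDs of 1.4 and 1.7, α = 0.05 and a printed β of 0.95. The result is 45 per condition, raised to 50 for 10% drop-out.

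Section 8.2 applies a repeated-measures ANOVA to "possible differences in gut flora, fat absorption, REE, activity and body composition between the four groups", with Scheffe's test post hoc and one significance threshold of p < .05.

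**The concern.** Sections 4.4 and 6.1.1 each announce the primary endpoint of the study and then give different lists. Someone writing the analysis plan or the report could not tell which list decides the trial. The choice could then be made, or appear to have been made, after the results were known.

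The power statement is attached to the wrong thing. A reader of Section 4.4 meets gut flora and fat absorption as primary and then a 95% power figure, and will take the figure to cover them. It was derived from body weight, which that section does not call primary.

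With several primary endpoints, one common threshold and no statement of how they combine, the trial's false-positive rate is also undefined.

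**Working it through.** **1. The endpoint sets side by side**

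| Domain | Summary | Section 2 (primary aim) | Section 4.4 | Section 6.1.1 | Section 6.1.2 |
|---|---|---|---|---|---|
| Gut flora | main | primary | primary | primary (F/B ratio) | – |
| Fat absorption / faecal fat | main | primary (fat metabolism) | primary | primary (total faecal fat) | – |
| Body weight | not named | primary | not named | primary | – |
| Body composition | main | – | – | – | secondary |
| REE | main | – | – | – | secondary |

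The primary aim in Section 2 matches Section 6.1.1 in substance: Section 2 also names the Firmicutes/Bacteroidetes (F/B) ratio, and both sections use faecal fat as the measure of lipid absorption. That leaves about three distinct sets. The direct conflicts are body weight (primary in 6.1.1, absent from 4.4) and REE and body composition (main in the Summary, secondary in 6.1.2).

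**2. What the power figure refers to**

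Inputs from Section 4.4: difference 72.5 − 71.4 = 1.1; variance sum 1.4² + 1.7² = 1.96 + 2.89 = 4.85; common SD √(4.85/2) = 1.557; standardised difference 1.1/1.557 = 0.706. The printed β of 0.95 is read as power 0.95.

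Printed formula: N = 2 + (z for power + z for α)² × 4.85/1.1², where 4.85/1.21 = 4.008.

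- One-sided α = 0.05: 2 + (1.645 + 1.645)² × 4.008 = 2 + 43.4 = 45.4. The t-test calculation gives 45.
- Two-sided α = 0.05, as the printed α/2 requires: 2 + (1.645 + 1.960)² × 4.008 = 2 + 52.1 = 54.1. The t-test calculation gives 54.

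The plan's 45 therefore reproduces from the body weight inputs, but only with a one-sided α. No mean, difference or SD is given for the F/B ratio or faecal fat, so power for them cannot be computed.

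**3. Body-weight power at 45 per arm**

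The noncentrality is 0.706 × √(45/2) = 3.35. The normal approximation to power is Φ(3.35 − critical value).

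| Two-sided level | Critical value | Normal approximation | t-test |
|---|---|---|---|
| 0.05 | 1.960 | 91.8% | 91.2% |
| 0.05/3 = 0.0167 (first Holm step) | 2.394 | 83.1% | 81.6% |

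On the one-sided reading, the t-test figures are 95.4% at 0.05 and 88.1% at 0.0167. Keeping 95% at a two-sided 0.0167 would take 67 per arm before drop-out.

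**4. False-positive rate if any one success counted**

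For k independent endpoints, each tested once at 0.05, the chance of at least one false positive is 1 − 0.95^k.

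- k = 2 (Section 4.4): 1 − 0.9025 = 9.75%
- k = 3 (Section 6.1.1): 1 − 0.8574 = 14.3%
- k = 4 (Summary): 1 − 0.8145 = 18.5%

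Scheffe's test does not change these figures. It protects contrasts among the four groups within one outcome, not claims across outcomes.

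**The case against.** Several stronger readings are tempting, and the protocol does not support them.

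- **Four different definitions.** Section 2 states an aim, and its domains are those of 6.1.1. About three sets remain, and the two domains in 4.4 are contained in 6.1.1.
- **Any single success makes the trial positive, so the error rate is well above 5%.** Section 8.2 sets a threshold and no success rule. If all endpoints had to succeed, there would be no inflation. The percentages above are conditional.
- **The rate is higher still because of time, group and interaction tests at two visits.** Section 8.2 describes one repeated-measures model per outcome, not separate tests by visit. A time effect alone says nothing about green tea, and post hoc group contrasts fall under Scheffe.
- **Body weight is never analysed.** Section 8.2 does not name it but lists body composition. Section 6.3.1, which carries that title, opens with body weight, and BMI is counted there too. The wording is loose; it is not a proven omission.

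It is also fair that a rule across endpoints is often left to the statistical analysis plan, which is not at hand. The absence of such a rule would not carry the point alone.

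What the objection does not remove is that the protocol itself names its primary endpoint in conflicting ways and ties its power figure to a variable outside the list in the same section. An analysis plan cannot settle that without choosing between protocol statements.

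**Conclusion.** The point holds in this form. The Summary, Section 4.4 and Section 6.1.1 give about three conflicting sets of main endpoints, and the Summary also contradicts Section 6.1.2 on REE and body composition. The only power calculation concerns body weight, so the 95% figure says nothing about the F/B ratio or faecal fat.

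The success rule across endpoints is unspecified, which is not the same as a demonstrated inflation. Rates of 9.75%, 14.3% and 18.5% would follow only if one positive endpoint out of two, three or four were claimed as success, with independent endpoints and one test each. Positive correlation would lower them.

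The power figures rest on the means and SDs in Section 4.4, a two-group comparison and 45 analysed per arm.

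This should be corrected before outcome data are examined, because afterwards the choice of list can no longer be shown to be independent of the results.

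**What to change.** 1. Use the Section 6.1.1 list (F/B ratio, total faecal fat, body weight) in the Summary, Section 4.4 and Section 8.2. Name body weight explicitly in 8.2, and keep REE and body composition secondary throughout.
2. State in Section 4.4 that the power figure applies to body weight only.
3. Prespecify one error-control rule for the green tea versus placebo comparison: either a single primary endpoint at two-sided 0.05 with the rest secondary, or Holm across the three at an overall two-sided 0.05.
4. Restate the power. With 45 per arm and the Section 4.4 inputs, body-weight power is about 91% at two-sided 0.05 and about 82% at the first Holm step, against the 95% claimed. The Holm figure is a floor, since a later step uses a larger level. Enrolment need not rise.

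The amendment changes text only: no visit, measurement or treatment is affected. Its price is statistical. A single primary endpoint costs the other two their primary status; Holm keeps all three but costs about 9 to 10 percentage points of body-weight power at the first step (91.2% − 81.6%).

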#### 6.1.2. Secondary study parameters/endpoints

- Resting energy expenditure (REE)
- Respiratory quotient (RQ)
- Three frequency eating questionnaire (TFEQ)
- Body composition: BMI, body fat percentage, fat mass index (FMI)
- Body fat distribution: waist circumference, waist-to-hip ratio (WHR)

### 6.2. Randomisation, blinding and treatment allocation

The study will be conducted in a randomized, placebo-controlled, double-blind parallel design with four randomly sequenced experimental conditions. Randomisation will take place using a computerized randomization program ('Randomizer' macro in Excel).

### 6.3. Study procedures

#### 6.3.1. Body composition

Body weight will be measured using a digital balance and height by a wall-mounted stadiometer. BMI will be calculated as body weight (kg) divided by height (m) squared. The deuterium dilution method according to the Maastricht protocol will be used to determine total body water (TBW) (13). The subjects will be asked to collect a urine sample in the evening just before drinking a deuterium-enriched water solution. After ingestion of this solution, the subject will go to bed and no additional consumption is allowed for that period. Ten hours after drinking the water solution, another urine sample will be collected. The dilution of the deuterium isotope is a measure of the TBW of the subject. Fat mass (FM) will be calculated as body weight minus TBW divided by the hydration factor 0.73 (14). Additionally, fat mass will be determined by Bodpod measurements. Fat mass index (FMI) will be calculated by fat mass (kg) divided by height (m) squared. BMI, FM (%) and FMI will be used to define body composition. Waist and hip circumference will be determined in standing position by a tape measure. Waist circumference will be measured at the smallest circumference between rib cage and iliac crest, and hip circumference at the level of the spina iliaca anterior superior.

Accordingly, WHR will be calculated by dividing waist by hip circumference. Both waist circumference and waist-to-hip ratio will be used to define different patterns of body fat distribution.

#### 6.3.2. *Attitude toward eating.*

To determine whether attitude toward food intake changed during the experiment, the three-factor eating questionnaire was used. Factor 1 indicates cognitive dietary restraint, factor 2 indicates disinhibition of eating, and factor 3 indicates general hunger feelings.

#### 6.3.3. *REE and substrate oxidation.*

REE and substrate oxidation will be measured by means of an open-circuit-ventilated hood system. After 30 min of resting, to make sure that the subjects are rested, REE will be measured in the morning with subjects in a fasted state while lying supine for 30 min. Gas analyses will be performed by a paramagnetic oxygen analyzer (OmniCal type 1155B; Servomex, Crowborough Sussex, United Kingdom) and an infrared carbon dioxide analyzer (OmniCal type 1520/1507; Servomex). Calculation of REE is based on Weir's formula (15). Respiratory quotient will be calculated as carbon dioxide produced/oxygen consumed. Alternately, before or after each REE measurement, the function of the ventilated-hood system will be checked with methanol burning during 20 min. The methanol burner will be set to burn 0–2 g/min, which is equivalent to the production of 150 mL CO2/min and the consumption of 225 mL O2/min. Because an error percentage depends on burn rate, the expression of the error limit in absolute mL/min is preferred; hence, the limit values of 7–5 mL CO2 and 11 mL O2/min, respectively (5% of 150 mL CO2 and 5% of 225 mL O2).

#### 6.3.4. *Physical activity*

The subjects will be instructed to maintain their habitual activity level. Physical activity will be determined with the use of a triaxial accelerometer for movement registration (Tracmor; Philips, Eindhoven, Netherlands) during three weeks (baseline, week 6 and week 12). The Tracmor is a small device (7 × 2 × 0.8 cm; 30 g), which measures accelerations in the anteroposterior, mediolateral, and vertical directions of the trunk (16). Subjects will wear the same type of accelerometer during waking hours in a belt at the back of the waist, during the three weeks.

PAL (physical activity level) will be calculated with the following equations:

$$TEE = -1.259 + (1.552 \times REE) + (0.076 \times \text{counts/min})$$

$$PAL = TEE/REE$$

in which TEE (total energy expenditure) and REE are measured in MJ/d.

#### 6.3.5 Energy expenditure

TEE will be calculated as indicated above.

#### 6.3.6. Energy intake and food choice

Subjects will be asked not to change their food pattern during the period of twelve weeks. However, they will be instructed to abstain from caffeine-rich products like tea, coffee, cola-type soft drinks and energy drinks and not to use dairy products (like milk, cheese, pudding and yoghurt) because consumption of milk-protein inhibits the effect of green tea on diet induced thermogenesis (DIT) (17). To determine whether subjects did not change their food pattern, except as instructed, during the period of twelve weeks they will be asked to fill in a food frequency questionnaire at each visit. During the last four days before the first visit subjects will be asked to maintain their food pattern and to record all the food and drinks they consume. Then, during the last four days before the next visits subjects will be asked to eat and drink the same as on the days four days before the first visit.

#### 6.3.7 Faecal energy, faecal fat and faecal FA composition

All faeces excreted will be collected in preweighed containers during the last three days before each visit. Faeces will be collected during three days according to the standard operating procedure of clinical chemistry. Furthermore, reference values are based on 3x24h faeces. Before analysis, the faecal samples will be freeze-dried and homogenized. For each subject, samples from the same period will be pooled. Faecal energy will be obtained using a bomb calorimeter (Ika-calorimeter system C4000; Heitersheim, Germany). Total faecal fat will be analyzed after the method of Bligh and Dyer (18) with modifications. Before fat extraction, the faecal samples will be acid hydrolyzed with 3 N HCl at 80°C for 1h. During extraction, a known quantity of 17:0 (Sigma H-4515) will be added to all samples as an internal standard for the FA analysis. The faecal FA composition will be determined as described below. The extracted fat will be saponified with 0.8ml methanolic sodium hydroxide (0.5M) by heating at 100°C for 1h. The FAs will be hydrolyzed by the addition of 1ml of boron trifluoride/methanol complex (20%) and methylated by heating at 100°C for 45min. The methyl esters will be extracted by 2ml heptane mixed with 4ml of saturated sodium chloride solution. Finally, the heptane phase will be transferred to vials. The FA methyl esters will be analyzed by gas chromatography (HP 6890series GC system; Agilent Technologies, Palo Alto, CA, USA). The gas chromatograph will be equipped with an automatic on-column injector (HP 7673) (split ratio 4.325:1), a capillary column of 30m × 320µm inner diameter,

0.25µm film thickness (Omegawax; Supelco 4-293-415) and a flame ionization detector. Helium will be used as the carrier gas. The oven temperature will be set at 86°C, 4min isothermal, 10°C min to 210°C, 15min isothermal. The detector will be set at 250°C. Chromatograms will be recorded with a data system integrator (HP Chemstation; Hewlett-Packard, Palo Alto, CA, USA). Identifications of peaks will be made by comparison of the retention times with those of a standard (mix of pure FAs from Sigma-Aldrich, Broendby, Denmark and Merck & Co Inc., NJ, USA) run under identical conditions. The quantity of FAs in each sample will be calculated from the known quantity of internal standard by comparing the area under the curve of each FA methyl ester with that of 17:0 methyl ester. Conjugated and free BAs in faecal samples will be quantified by reversed-phase high-performance liquid chromatography with pulsed amperometric detection as outlined by Dekker et al. (19). The freeze-dried samples will be mixed using a Shaker VXR vibrax (IKA-Werke, Staufen, Germany) at 1500 r.p.m. for 30 s and subsequently centrifuged at 5000 g for 10 min. The supernatant will be passed through a nylon syringe filter membrane (Cameo 17N-DDR02T17NB) before injection onto the high-performance liquid chromatography. The chromatographic conditions that will be used are described by Knarreborg (20).

